#### **4.3.2 Secondary Endpoints**

- (1) Composite of cardiovascular death, hospitalization for HF, non-fatal stroke, or non-fatal myocardial infarction;
- (2) Changes from baseline to 6 months in the following parameters:
  - a) Echocardiography: LVEF, LVEDD;
  - b) Cardiac magnetic resonance (CMR): LVEF, left ventricular end-diastolic volume index (LVEDVi), left ventricular global longitudinal strain (LV-GLS), and percentage of late gadolinium enhancement (LGE);
  - c) NT-proBNP;
  - d) KCCQ-12 score;
  - e) Heart rate;
  - f) Systolic blood pressure;
  - g) Diastolic blood pressure.
- (3) Recurrence of atrial tachyarrhythmia and atrial tachyarrhythmia burden;
- (4) Adverse drug events, including symptomatic hypotension, renal dysfunction, hyperkalemia, bradycardia, diabetic ketoacidosis and urogenital infection.

Definitions: 1) renal dysfunction: a decrease in the eGFR of  $\geq 50\%$  or a decrease of  $>30$  mL/min/1.73 m^2 from randomization to  $<60$  mL/min/1.73 m^2; 2) hyperkalemia: serum potassium  $>5.5$  mmol/L; and 3) bradycardia: heart rate at rest  $<40$  beats/min.

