### **3. Study Objective**

To compare the feasibility and safety of stepwise withdrawal of HF guideline-directed medical therapy (GDMT) versus continued GDMT therapy in patients with AF and improved cardiac function after successful catheter ablation (suspected AMC).

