### **4.3 Study Outcomes**

#### **4.3.1 Primary Endpoint**

HF deterioration within 6 months.

Defined as meeting any of the following criteria:

(1) A decrease in LVEF on echocardiography by >10% in absolute value and to <55%;

- (2) An increase in LVEDD on echocardiography by >10% and exceeding the normal range;
- (3) A twofold rise in NT-proBNP and to >400 ng/L;
- (4) None of the above criteria are met, but worsening HF signs and/or symptoms are present,, as adjudicated by the research team.

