#### 4.4.3 Specific Conditions:

1) Hypertension in GDMT withdrawal group: For newly developed hypertension or elevated blood pressure during follow-up, calcium channel blockers were used as substitutes. If patients continued to have elevated blood pressure while on calcium channel blockers, ARNi/RASi or beta-blockers could be reinitiated as appropriate.

2) Hypotension: Medication doses may be adjusted downward as clinically indicated.

3) Diabetes in GDMT withdrawal group: Diabetes therapy was adjusted to avoid SGLT2 inhibitors. If patients continued to have elevated blood glucose despite treatment with metformin combined with a dipeptidyl peptidase-4 inhibitor or an alpha-glucosidase inhibitor, SGLT2 inhibitors could be reinitiated.

4) Rapid Ventricular Rate: If ventricular rate exceeds 100 bpm in sinus rhythm or >110 bpm in AF/AFL or palpitation,  $\beta$ -b may be initiated or up-titrated as appropriate.

5) Others: Medication adjustments will be made based on guideline recommendations and clinical judgment.

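### Secondary endpoint (4) names only effects of taking heart failure drugs; the non-HF effects of stopping that section 4.4.3 anticipates are not compared as events

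*Protocol*

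**What the plan says.** The objective in Protocol section 3 is "To compare the feasibility and safety of stepwise withdrawal of HF guideline-directed medical therapy (GDMT) versus continued GDMT therapy". The endpoints that bear on safety are:

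- Primary (4.3.1): "HF deterioration within 6 months", triggered by LVEF, LVEDD or NT-proBNP, or, failing these, where "None of the above criteria are met, but worsening HF signs and/or symptoms are present".
- Secondary (1) (4.3.2): "Composite of cardiovascular death, hospitalization for HF, non-fatal stroke, or non-fatal myocardial infarction".
- Secondary (2): change from baseline to 6 months in imaging measures, NT-proBNP, KCCQ-12, heart rate, and systolic and diastolic blood pressure.
- Secondary (3): "Recurrence of atrial tachyarrhythmia and atrial tachyarrhythmia burden".
- Secondary (4): "Adverse drug events, including symptomatic hypotension, renal dysfunction, hyperkalemia, bradycardia, diabetic ketoacidosis and urogenital infection".

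Section 4.4.3 then sets out how certain conditions are handled. In the withdrawal group, "For newly developed hypertension or elevated blood pressure during follow-up, calcium channel blockers were used as substitutes", and ARNi/RASi or beta-blockers may be restarted if pressure stays high. Also in that group, diabetes treatment is changed to avoid SGLT2 inhibitors, which may be restarted if glucose stays high. In either arm, "If ventricular rate exceeds 100 bpm in sinus rhythm or >110 bpm in AF/AFL or palpitation", a beta-blocker may be started or increased.

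**The concern.** The trial sets out to compare the safety of two strategies, and each has its own side effects. Those of continuing are listed by name as an endpoint. Those of stopping, apart from HF and major cardiovascular or arrhythmic events, appear only as conditions to be managed.

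The protocol is also uneven within single variables. Blood pressure and heart rate changes are already endpoints, yet symptomatic hypotension and bradycardia are counted as events as well. The low direction therefore gets both a mean change and an event count, while the high direction gets only the mean change. If endpoint (4) is quoted as the tolerability result, withdrawal may look better tolerated partly because its own non-HF effects were not on the list.

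**Working it through.** **Step 1: count the named events.** Hypotension, renal dysfunction, hyperkalaemia, bradycardia, ketoacidosis and urogenital infection: 6 of 6 are effects of taking HF drugs, 0 of 6 are effects of stopping them.

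**Step 2: see whether another endpoint picks up the conditions in 4.4.3.**

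| Endpoint | Raised blood pressure | Raised glucose | Rapid ventricular rate |
|---|---|---|---|
| Primary | only if HF worsens | only if HF worsens | only if HF worsens |
| Secondary (1) | only through death, HF admission, stroke or MI | same | same |
| Secondary (2) | value at 6 months | no | value at 6 months |
| Secondary (3) | no | no | the atrial arrhythmia, not its rate; not sinus rhythm |
| Secondary (4) | not named | not named | not named |

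**Step 3: see what the 6-month change can show.** By month 6 a patient whose pressure rose may be on a calcium channel blocker, or back on ARNi/RASi or a beta-blocker. A patient with a fast rate may be on a beta-blocker. An effect that occurred and was treated can then read as no change. For glucose there is no measurement at all: it is absent from the biochemistry and urinalysis items in 4.5.2.1 and from the monthly tests in 4.5.2.3.

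**Step 4: illustrate the sensitivity.** There is no planned figure to reproduce. Section 5.1 takes the 50 patients (25 per arm) from a precedent trial and gives no rates, effect or power. All rates below are assumptions.

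- Listed on-drug events: 5% withdrawal, 20% continuation. Difference 5 − 20 = −15 points (negative favours withdrawal).
- Withdrawal-type events: 10%, 20% or 30% in the withdrawal arm, 5% in the continuation arm, independent of the first kind.
- Any event = 1 − (1 − on-drug rate) × (1 − withdrawal-type rate).
- Continuation: 1 − 0.80 × 0.95 = 24.0%.
- Withdrawal: 1 − 0.95 × 0.90 = 14.5%; 1 − 0.95 × 0.80 = 24.0%; 1 − 0.95 × 0.70 = 33.5%.
- Differences: −9.5, 0.0 and +9.5 points.

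The sign depends on the assumed withdrawal-type rate, which the named event endpoints would not estimate.

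**Step 5: check how much endpoint (4) can show by itself.** With 25 per arm and the two-sided Fisher test allowed by 5.3.2, 0 versus 5 events gives p = 0.0502 and 0 versus 6 gives p = 0.022. Power for 5% versus 20% is about 20%. Endpoint (4) is weak evidence in either direction and will be read mainly as counts.

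**The case against.** A reader might infer that the safety comparison as a whole is tilted towards withdrawal. The documents do not support that. The primary endpoint is the main harm expected from stopping, and it can be met on signs and symptoms alone. Secondary endpoints (1) to (3) can also go against withdrawal. Section 10.1.2 itself lists the components of the composite among potential study-related adverse events, so endpoint (4) is not the only adverse-event endpoint. Section 2 gives drug side effects as a reason for the trial, so endpoint (4) is a fair measure of the hoped-for benefit of stopping. All of this stands and limits the point.

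A reader might also infer that patients in the withdrawal arm cannot have the listed events. They can. Under 4.4.1 one drug is adjusted every two weeks. Take a patient on all five classes, with beta-blocker and ARNi/RASi at full target dose and the rest at stopping dose. That patient needs 1 + 1 + 3 + 3 + 1 = 9 steps, the last at week 8 × 2 = 16 of about 26. Drugs may later be restarted, and low heart rate, renal decline or high potassium can occur without HF drugs. Hence favourable or neutral in expectation, not by necessity.

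Three further objections stand in part:

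- Sections 10.1 and 10.3 require every adverse event to be recorded and analysed, and endpoint (4) is open-ended. The information is therefore not lost, and a table by arm may properly sit in the SAP. But an endpoint headed as adverse drug events does not naturally take in hypertension after a drug is stopped.
- Rapid ventricular rate in 4.4.3 is not restricted to the withdrawal arm, so it is not purely an effect of stopping. Counting it in both arms deals with this.
- Counting every new blood pressure or glucose drug as harm would score protocol-directed substitution against one arm only. The fix leaves it out.

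**Conclusion.** The point holds in a limited form and is of minor to moderate weight. Endpoint (4) runs in one direction. Raised blood pressure, raised glucose and rapid ventricular rate, all anticipated in 4.4.3, are not compared as events, and the 6-month changes can hide an effect that was treated. The count of 6 against 0 and the missing glucose test are read directly from the text. The shift from −15 points to between −9.5 and +9.5 rests wholly on assumed rates and independence: it shows that the result is sensitive, not which way the trial will fall. The documents support no conclusion that the overall design favours withdrawal.

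**What to change.** Keep endpoint (4) and label it as on-drug adverse events, the expected benefit of stopping. Add a parallel prespecified list of off-drug events, counted at any time up to 6 months in both arms:

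- blood pressure above 160/100 mmHg, the figure in exclusion criterion 6 of 4.2.2, stating whether either component suffices;
- resting ventricular rate above 100 bpm in sinus rhythm or above 110 bpm in AF/AFL, the figures in 4.4.3;
- reported separately as open-label: restart of ARNi/RASi, beta-blocker or SGLT2 inhibitor for blood pressure, rate or glucose.

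Do not count the first protocol-directed substitution (a calcium channel blocker, or a glucose-lowering drug replacing an SGLT2 inhibitor) as harm. Report by arm the on-drug list, the off-drug list and any event of either kind, the last with and without the restart events. The thresholds serve only to count events and change no treatment rule.

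The cost is endpoint wording and one more table. Daily blood pressure and heart rate, and monthly vital signs, Holter and medication, are already recorded (4.5.1, 4.5.2.3). The protocol does not mention recording the reason for a restart, so that needs a field. Two weaknesses remain: restarts depend partly on open-label prescribing, and a pressure rise treated before it passes 160/100 mmHg goes uncounted.

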#### **4.4 Intervention**

The intervention group will undergo a protocol-defined, stepwise withdrawal of HF medications, while the control group will continue GDMT for HF. Apart from the intervention under investigation, the management of AF/AFL and other non-HF comorbidities will be conducted in accordance with clinical guidelines for both groups. The investigators will evaluate and manage adverse drug events appropriately, which may include dose reduction or discontinuation of the offending medication.

##### **4.4.1 Stepwise GDMT Withdrawal Group Protocol:**

medications were reduced or discontinued stepwise every 2 weeks, with one medication adjusted at a time. For patients on  $>20$  mg spironolactone,  $>10$  mg finerenone,  $>40$  mg furosemide, or  $>25\%$  of ARNi/RASi or beta-blockers target doses, dosages were reduced by

50% every two weeks. Medication doses at or below these thresholds and SGLT2 inhibitors, were discontinued immediately. The withdrawal sequence was: loop diuretics, MRAs, beta-blockers, ARNi/RASi, and SGLT2 inhibitors. GDMT was reinitiated if the primary endpoint occurred.

#### 4.4.2 Continuation Therapy Group Protocol:

GDMT type and dosage were maintained throughout follow-up

#### 4.4.3 Specific Conditions:

1) Hypertension in GDMT withdrawal group: For newly developed hypertension or elevated blood pressure during follow-up, calcium channel blockers were used as substitutes. If patients continued to have elevated blood pressure while on calcium channel blockers, ARNi/RASi or beta-blockers could be reinitiated as appropriate.

2) Hypotension: Medication doses may be adjusted downward as clinically indicated.

3) Diabetes in GDMT withdrawal group: Diabetes therapy was adjusted to avoid SGLT2 inhibitors. If patients continued to have elevated blood glucose despite treatment with metformin combined with a dipeptidyl peptidase-4 inhibitor or an alpha-glucosidase inhibitor, SGLT2 inhibitors could be reinitiated.

4) Rapid Ventricular Rate: If ventricular rate exceeds 100 bpm in sinus rhythm or >110 bpm in AF/AFL or palpitation,  $\beta$ -b may be initiated or up-titrated as appropriate.

5) Others: Medication adjustments will be made based on guideline recommendations and clinical judgment.

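### Sections 4.4.1 and 4.4.3 do not agree on when HF drugs may be restarted, and a restart for suspected HF without symptoms and below the thresholds would not be counted in the primary endpoint

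*Protocol*

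**What the plan says.** **When drugs go back on.** Protocol section 4.4.1 ends the withdrawal schedule with "GDMT was reinitiated if the primary endpoint occurred". It does not say that this is the only case. Section 4.4.3 then lists other routes. In the withdrawal group, for persistent high blood pressure, "ARNi/RASi or beta-blockers could be reinitiated as appropriate". For persistent high glucose, "SGLT2 inhibitors could be reinitiated". For a fast ventricular rate or palpitation, a beta-blocker "may be initiated or up-titrated as appropriate". Item 5, headed as covering other matters, closes the list: "Medication adjustments will be made based on guideline recommendations and clinical judgment". It names no trigger, drug or arm.

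**What counts as an event.** Section 4.3.1 has four alternative criteria:
- Criterion 1: "A decrease in LVEF on echocardiography by >10% in absolute value and to <55" per cent.
- Criterion 2: "An increase in LVEDD on echocardiography by >10% and exceeding the normal range".
- Criterion 3: NT-proBNP doubled and above 400 ng/L.
- Criterion 4: "None of the above criteria are met, but worsening HF signs and/or symptoms are present", adjudicated by the research team.

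No criterion, and no secondary endpoint in section 4.3.2, counts a restart of HF drugs.

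**Setting.** The trial is open-label (4.1). NT-proBNP and echocardiography are repeated monthly (4.5.2.3). HF medications are recorded at every visit (4.5.1). The continuation group keeps drug type and dose (4.4.2). Patients not lost to follow-up are analysed as randomised (4.7.1).

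**The concern.** The endpoint and the treatment rules interact. If item 5 permits a restart on suspicion of HF, the investigator can act on a monthly echocardiogram or NT-proBNP result that is worsening but has not crossed a threshold. If the restart works, the threshold is never crossed and the patient is counted as free of HF deterioration.

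The decision is made with knowledge of the arm. Withdrawal patients are the ones with stopped drugs to put back, so events averted in this way would come mostly from that arm. The trial asks whether withdrawal is safe and is meant to inform a larger trial. An undercount of failures in the withdrawal arm would affect the main safety comparison and any event rate carried forward from it.

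**Working it through.** **1. The restart rules side by side.** Section 4.4.1 gives a condition under which GDMT is restarted, but does not make it exclusive. Items 1, 3 and 4 of section 4.4.3 show that it is not exclusive, since they allow restarts without an endpoint for blood pressure, glucose and rate. Item 5 neither mentions nor excludes HF. So the text does not settle whether a restart for suspected HF before an endpoint is allowed.

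**2. Which restarts would go uncounted.** A restart prompted by worsening HF signs or symptoms should count under criterion 4, if so adjudicated. The gap concerned here is decline without signs or symptoms that stays below criteria 1 to 3. From those criteria and the entry limits (LVEF at least 55%, NT-proBNP below 250 ng/L):

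| Baseline | Level needed for an event |
|---|---|
| LVEF 55% | below 55 − 10 = 45% |
| LVEF 60% | below 60 − 10 = 50% |
| LVEF 65% | below 65 − 10 = 55% |
| LVEF 70% | below 55% (a 15-point fall) |
| NT-proBNP 100 ng/L | above 400 (fourfold) |
| NT-proBNP 200 ng/L | above 400 (twofold) |
| NT-proBNP 249 ng/L | 2 × 249 = 498 |

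**3. A worked patient.** Baseline LVEF 62% and NT-proBNP 110 ng/L, both eligible. At a monthly visit they are 53% and 380 ng/L, LVEDD has not met criterion 2, and there are no worsening signs or symptoms.
- Criterion 1: 62 − 53 = 9 points, not more than 10. Not met.
- Criterion 3: 380/110 = 3.5-fold, but 380 is below 400. Not met.
- Criterion 4: needs worsening signs or symptoms. Not met.

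If treatment is restarted now and no criterion is met later, this patient is a non-event.

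**4. Effect of one averted event.** Inputs: 25 per arm (Protocol Summary); two-sided test, significance at P ≤ 0.05, chi-squared or Fisher (5.3.2). The risk shift is 1/25 = 4 percentage points. When all k events fall in one arm, two-sided Fisher p = 2 × C(25,k)/C(50,k):
- 6 v 0: 2 × 177,100/15,890,700 = 0.022
- 5 v 0: 2 × 53,130/2,118,760 = 0.0502

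This depends on the test. Uncorrected chi-squared for 5 v 0 is 50 × 125²/(25 × 25 × 5 × 45) = 5.56, p = 0.018, so there would be no reversal. The expected event count there is 2.5 per arm, where Fisher is the usual choice. At 8 v 2 the expected event count is 5 per arm, and the tests disagree: Fisher p = 0.074, uncorrected chi-squared 50 × 150²/(25 × 25 × 10 × 40) = 4.5, p = 0.034.

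**5. Scale under assumed rates.** Section 5.1 gives no event rates, effect size or power, so the sample size of 50 cannot be reproduced. The rates below are assumptions. Observed withdrawal rate = true rate × (1 − share averted and uncounted), with a true rate of 30%. Exact Fisher power, 25 per arm:

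| Share uncounted | Expected withdrawal events | Control 0% | Control 4% | Control 8% |
|---|---|---|---|---|
| 0 | 7.5 | 0.81 | 0.61 | 0.39 |
| 25% | 5.6 | 0.51 | 0.32 | 0.18 |
| 50% | 3.75 | 0.16 | 0.09 | 0.04 |

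This shows direction and sensitivity only. The model puts all averted events in the withdrawal arm, and nothing in the protocol says that the share is as high as 25% or 50%.

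**The case against.** **Item 5 may not be about HF.** It closes a list of mainly non-HF conditions and speaks of adjustments, not restarts. HF restart has its own rule in section 4.4.1. A natural reading is that item 5 covers other comorbidities. This stands in part: a restart for suspected HF is permitted only by open wording, so the point is an ambiguity to resolve.

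**Criterion 4 catches most rescues.** A reader might infer that any failing withdrawal can be rescued early and scored as a success. The protocol does not support that, because worsening signs or symptoms count even when no threshold is met. What remains is the symptom-free, below-threshold patient, and the worked example sits close to two limits. The residue is narrower, but real in a trial that looks for such changes every month.

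**The bias is not strictly one way.** A reader might infer that only the withdrawal arm can be affected. Item 5 is not limited to one arm, so on the open reading an HF drug could also be started or increased, uncounted, in a continuation patient. Section 4.4.2 makes this less likely but does not exclude it.

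**A supporting analysis belongs in the SAP.** Largely true, and its absence from the protocol is not the criticism. The protocol does fix both the endpoint and the restart wording. The reason for a drug change must be captured at the time; the visit schedule shows medications recorded, but does not show reasons.

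**This is a pilot, and the event counts are chosen at the boundary.** Both true. The p-values show fragility and are not a forecast.

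**Conclusion.** The concern holds in a limited form. Sections 4.4.1 and 4.4.3 leave open whether HF drugs may be restarted for suspected HF before an endpoint, and must be reconciled; no view is taken on which clinical rule is right. If such restarts are allowed, those in symptom-free patients below criteria 1 to 3 are uncounted and are decided with knowledge of the arm. The resulting bias is mainly, but not only, toward withdrawal looking safe.

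Its size cannot be estimated from the protocol. The firm figure is 4 percentage points of arm risk per averted event, assuming all 25 patients in the arm are analysed. The change from p = 0.022 to p = 0.0502 assumes Fisher's test and counts of 6 v 0 and 5 v 0. The point merits action because the remedy is cheap and the reason for a restart may be hard to recover reliably afterwards.

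**What to change.** 1. Reconcile sections 4.4.1 and 4.4.3 item 5 so that the protocol states when restart is allowed. The content of that rule is a clinical decision for the investigators.
2. In both arms, record the reason for every start, restart or increase of an HF drug (suspected HF, blood pressure, rate, glucose, other), entered before the adjudication result is known.
3. Leave the primary endpoint and the clinician's freedom to treat unchanged. Report beside the primary result one prespecified supporting analysis in which a start, restart or increase for suspected HF counts as HF deterioration at that date, in either arm.

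**Cost:** clarified protocol text, one CRF field and one further analysis.

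**Downside, to be stated with the result:** these decisions are discretionary and made with knowledge of the arm, so cautious restarts can overstate events in the withdrawal arm. The primary result may err low for that arm and the supporting result high. Read them as a bracket; the supporting analysis does not replace the primary one.

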#### 4.4.4 Management of Atrial Tachyarrhythmia Recurrence

Throughout the 6-month follow-up period, if patients experience recurrence of atrial fibrillation or atrial flutter (AF/AFL), rhythm control strategies will be implemented in accordance with current clinical guidelines. These strategies include, but are not limited to: antiarrhythmic drug therapy, repeat catheter ablation, or cardioversion.

The occurrence of AF recurrence itself will not alter the GDMT withdrawal or continuation strategy. All patients will continue with their originally assigned protocol (GDMT withdrawal group or GDMT continuation group) according to randomization, with regular reassessment of cardiac function and clinical status.

### 4.5 Study Flow

#### 4.5.1 Study Flowchart

| Visit                      | 1                    | 2                          | 3  | 4  | 5  | 6  | 7  | 8  |
|----------------------------|----------------------|----------------------------|----|----|----|----|----|----|
| Case Report Form           | Screening assessment | Baseline/
Randomization |    |    |    |    |    |    |
| Time from
Randomization | -1w~0w               | 0w                         | 1m | 2m | 3m | 4m | 5m | 6m |

|                                  |   |   |   |   |   |   |   |   |
|----------------------------------|---|---|---|---|---|---|---|---|
| Informed consent                 | ▲ |   |   |   |   |   |   |   |
| Demographics                     | ▲ |   |   |   |   |   |   |   |
| Medical history                  | ▲ |   |   |   |   |   |   |   |
| Vital signs                      | ▲ | ▲ | ▲ | ▲ | ▲ | ▲ | ▲ | ▲ |
| Laboratory tests                 | ▲ | ▲ | ▲ | ▲ | ▲ | ▲ | ▲ | ▲ |
| 24-hour Holter ECG               | ▲ | ▲ | ▲ | ▲ | ▲ | ▲ | ▲ | ▲ |
| Echocardiography                 | ▲ | ▲ | ▲ | ▲ | ▲ | ▲ | ▲ | ▲ |
| CMR                              | ▲ |   |   |   |   |   |   | ▲ |
| KCCQ score                       | ▲ |   |   |   |   |   |   | ▲ |
| HF medications                   | ▲ | ▲ | ▲ | ▲ | ▲ | ▲ | ▲ | ▲ |
| Other cardiovascular medications | ▲ | ▲ | ▲ | ▲ | ▲ | ▲ | ▲ | ▲ |

